**Exploratory Hypotheses:** NLP-ML-based characterization of temporal trends in functional outcomes, symptoms, physical health, and treatment will be correlated with structured clinical measures of the corresponding constructs, and will differentiate the above prospectively discovered longitudinal outcome trajectory subtypes. Through this, it is anticipated that NLP-ML-based temporal trends in functioning will serve as antecedent markers that inform prospective outcome trajectories.

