**3.1 Participants**

Participants will be eligible for this study if they: 1) are 16 years of age and older; 2) have a DSM-5 diagnosis of any schizophrenia spectrum disorder (SSD; e.g., schizophrenia, schizoaffective disorder, schizophreniform disorder, brief psychotic disorder, delusional disorder, unspecified schizophrenia spectrum or other psychotic disorder, other specified schizophrenia spectrum and other psychotic disorder, substance/medication-induced psychotic disorder), or related psychotic disorders (including bipolar I disorder with psychotic features or major depressive disorder with psychotic features); and 3) have adequate fluency in English to participate in clinical care without the need for a translator . Of note, participants will be eligible regardless of duration of illness, co-morbid mental or physical health conditions, capacity to consent to treatment, or whether they are receiving inpatient or outpatient services at CAMH. Participants will provide written informed consent, and for those individuals deemed incapable to consent to treatment by their treatment team and have a substitute decision-maker (SDM), their SDM will provide written informed consent in conjunction with participant assent to study participation. These broad eligibility criteria will serve to support generalizability of the sample and maximize the opportunity to evaluate the influence of common co-occurring illnesses on longitudinal outcome trajectories. Caregivers of study participants will also be invited to participate with the consent of the study participant.

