**3.9.6 Data Analysis**

Descriptive statistics will be used to characterize outcomes and covariates. Balance between groups will be assessed. Based on the type and distribution of the outcome data appropriate regression models will be fit accounting for the matched nature of these data.

*Cost analysis*

A standard ICES costing methodology and algorithm [(Wodchis et al., 2013, 2016)](https://www.zotero.org/google-docs/?IQrY21) will be used to estimate all health care costs incurred within the publicly funded provincial health care system. Costs will be identified for all hospitalizations (psychiatric and non-psychiatric), ED visits, physician visits (across all specialties), diagnostic tests, prescription drugs of those covered under via ODB, as well as other publicly funded services. Costs will be compared between comparison groups as well as between trajectories identified within the cohort.

**3.10 EMR-based Natural Language Processing (NLP) and Machine Learning (ML) for the characterization of longitudinal clinical course and outcomes**

Data will be extracted from the CAMH EMR and the Enterprise Data Warehouse for EMR-based retrospective characterization of the longitudinal clinical course and outcomes for study participants. Structured data elements that overlap with measures utilized for prospective cohort characterization (described above) will include sociodemographic data, administrative data related to treatment encounters, as well as clinical data (including diagnoses, medical problem lists, prescribed medications, laboratory data, anthropometric measures, and structured assessments of psychopathology (e.g., BPRS, CGI, BCATS) and functioning (e.g., WHO-DAS, PSP/SOFAS). In addition, free text clinical notes pertaining to consenting study participants will be also extracted.

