For Phase 2 analyses involving consenting study participants, once direct identifiers have been removed, the raw clinical notes for study participants will be shared with the study team, who will implement NLP methods in the R programming language to automatically convert the clinical notes into features. Converting the notes into features disrupts the order of the words and their context, or it reduces the text to numerical data representing various characteristics (e.g., polarity, semantics). For instance, the study team will generate a document-term matrix, containing words from the clinical notes as columns and their frequencies in each note as rows. This matrix will be utilized for topic modeling, an unsupervised ML algorithm to discover themes and generate temporal patterns and trends to investigate trajectories of outcomes and clinical phenomena in the study population. These temporal patterns will be linked with structured data for that participant available both from the EMR (including their age, sex, ethnicity, socioeconomic status, clinical and outcome measures where available (e.g., BPRS, CGI, WHO-DAS, PSP, B-CATS, AIMS, BARS, SARS), medication prescriptions, treatment encounters), as well as with the prospectively collected outcome, clinical, physical health, socioenvironmental, and biological data as part of this study.

We will store all study data (including data from the CAMH EMR, such as the structured data and de-identified clinical notes) on the CAMH Neuroinformatics platform for the entire duration of the study, and its availability will be restricted to the study team. The study team will use the remote server to access and analyze the data. If the study team wishes to use the data for purposes that were not outlined in the current version of the protocol, or if other individuals wish to access the data, the research team will submit an amendment or a new ethics application to the CAMH REB. The data will remain on the server, and it will never be downloaded on any computers or devices. The CAMH Neuroinformatics platform automatically tracks the activity of all its users; it keeps a record of individuals who log into the platform, the software they use, the data they access, and what they do with the data. This will allow for audits of who has accessed the document-term matrices and for what purpose these data were accessed.

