For Objective 2, we will associate the membership of the subgroups and thus the characteristics of these trajectories with sociodemographic and treatment factors, psychopathology, physical health, and biological measures at baseline by treating probabilistic membership as the dependent variable in the predictive models. We will apply structural equation modeling that combines the latent growth mixture model that determines the membership of the subgroups, measurement model that reduces the dimension of the predictors, and predictive model that links them into one step using simultaneous equations.

For objective 3, data analysis and outcomes are articulated in section 3.11, with further delineation taking place as part of the co-design process and pilot intervention designs.

For our exploratory objective, we will utilize correlational analyses to investigate relationships between temporal patterns emerging from topic modeling with study variables collected prospectively from study participants. We will also use general linear model analyses as appropriate to investigate differential characteristics between longitudinal outcome trajectory subtypes. These temporal patterns will also be examined as potential predictors for trajectory subtype membership in line with the methods employed for objective 2.

Overall retention rate is expected to fall within the acceptable range for statistical correction. Every effort will be made to prevent dropouts/missing data, and to complete relevant assessments for participants who drop out. Two statistical approaches, full information maximum likelihood estimation [(Arbuckle, 1996)](https://www.zotero.org/google-docs/?gONPAh) and multiple imputation methods [(Schafer, 1997)](https://www.zotero.org/google-docs/?Uh3flg) will be utilized when appropriate. As is typical in longitudinal research, we anticipate non-random missing data. Sensitivity analysis will be conducted to evaluate the impact of non-random missing data.

Sex and Gender Based Analysis

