Recruitment of participants for this study will take place across all outpatient and inpatient clinical services at CAMH where individuals with SSDs may be receiving care, and include both new and existing patients receiving clinical services. Sequential cohorts of participants will be recruited based on duration of illness, enabling an accelerated longitudinal design for this study that will serve to maximize coverage of longitudinal functional trajectories across illness stages. Through regular monitoring of participant recruitment, we will balance recruitment across these multiple cohorts. Core research assessments will mirror measurement-based care assessments and metabolic monitoring being implemented across these clinical services, with sharing of assessment results with the patient’s clinical team. All participants will be offered the opportunity to participate in the neuroimaging and additional laboratory/biological components of this study either as part of this study, or ideally through shared participation in existing complementary studies already taking place in the Division. Harmonization of study assessments and data sharing with existing clinical research studies will enable integration and collaboration across clinical research studies in the Division, maximize recruitment efforts, and leverage existing funded research studies for data collection. With regards to the potential participant pool from which individuals could be recruited, current patient volumes across Schizophrenia Division outpatient clinical services at CAMH, for example, indicate that over 4000 unique patients were seen over the past year, with an average of over 1900 patients seen per month. Based on these volumes, and the integration of study assessments for this proposed work within the context of routine clinical care for such patients within existing clinical services at CAMH, this study will aim to recruit 500 participants per year for 2 years, yielding a total sample of 1000 participants enrolled in this study (i.e., approximately 10 participants per week from over 15 outpatient and inpatient clinical services).

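### Exploratory objective: trends built from CAMH notes depend on contact with CAMH and start at first contact, so they can track outcome through service contact and record length rather than functioning

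*Protocol*

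**What the plan says.** Section 3.10 of the protocol names the source: "Data will be extracted from the CAMH EMR and the Enterprise Data Warehouse for EMR-based retrospective characterization of the longitudinal clinical course and outcomes". For consenting participants (Phase 2), the construction it describes is a document-term matrix "containing words from the clinical notes as columns and their frequencies in each note as rows". That matrix goes into an unsupervised topic model meant to "discover themes and generate temporal patterns and trends to investigate trajectories of outcomes and clinical phenomena in the study population".

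Section 1.1 gives the interpretation: it is anticipated that "NLP-ML-based temporal trends in functioning will serve as antecedent markers that inform prospective outcome trajectories". Section 5.0 gives the analysis. The patterns are correlated with prospectively collected variables, general linear models compare trajectory subtypes where appropriate, and the "temporal patterns will also be examined as potential predictors for trajectory subtype membership in line with the methods employed for objective 2".

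The population is broad. Under section 3.1, "participants will be eligible regardless of duration of illness", and eligibility does not depend on "whether they are receiving inpatient or outpatient services at CAMH". Under Recruitment and Sampling in section 5.0, recruitment will "include both new and existing patients receiving clinical services".

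Contact data are collected. In Phase 1, visit frequency, type and location are among the structured data used to check patterns found in the notes and to judge how representative the sample is. In Phase 2, treatment encounters are linked to the patterns. Neither section says that these data will be used to separate contact from clinical state.

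**The concern.** The text is observed only at CAMH contacts, which has two consequences.

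- **Irregular observation.** People with more contact contribute more text. If contact rises when someone is unwell, as seems likely, their text also over-represents unwell periods.
- **Truncation.** The record begins at first CAMH contact. An existing patient may have years of notes before enrolment, while a new patient has little or none, whatever the duration of illness. Section 2.5 describes electronic records as covering a person's lifetime, but one hospital's record does not. Section 3.9 itself accepts that hospitalizations and other contacts occur elsewhere.

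Section 5.0 recruits cohorts by duration of illness, so record length plausibly follows illness stage, which may in turn be related to trajectory. A note-based trend could then correlate with outcome, or help to predict class, partly because it stands in for service contact or tenure. What is at stake is the reading of a positive result as an antecedent marker of functioning.

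**Working it through.** The protocol states no sample size, power, note rate or error rate for the text objective, so there is no figure to reproduce. The mechanism follows from the text; its size can only be illustrated.

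**1. What follows from the protocol**

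- Source: the CAMH record only (3.10), so there is no text before first CAMH contact.
- Row of the described matrix: the note (3.10), so a period without contact has no row.
- Contact and tenure differ between people by design (3.1; Recruitment and Sampling in 5.0).
- Use: correlation and class prediction (5.0), read as antecedent information (1.1).
- Missing-data text (5.0): dropout and missed study assessments, not irregular notes.

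**2. Share of notes from one admission (all rates assumed)**

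Take 1,095 days, one admission of d days with k notes per inpatient day, and otherwise one outpatient note per 30.4 days:

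share = d·k / [d·k + (1,095 − d)/30.4]

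| Admission | Share of time | Outpatient notes | k = 1 | k = 2 | k = 3 |
|---|---|---|---|---|---|
| 30 days | 2.7% | 1,065/30.4 = 35.0 | 30/65.0 = 46% | 60/95.0 = 63% | 90/125.0 = 72% |
| 14 days | 1.3% | 1,081/30.4 = 35.6 | 14/49.6 = 28% | 28/63.6 = 44% | 42/77.6 = 54% |

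The result depends heavily on the outpatient rate. With weekly outpatient notes and k = 1:

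- 30 days: 30/(30 + 1,065/7) = 30/182.1 = 16%.
- 14 days: 14/(14 + 1,081/7) = 14/168.4 = 8%.

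**3. Simulation of the mechanism (all values assumed)**

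Monthly latent severity over 60 months is stationary (autocorrelation 0.8, SD 1), with no long-run trend. Notes are Poisson with mean 0.5·exp(b × severity) per month. The symptom share of a note is logistic(−1 + severity).

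- *Notes denser when unwell.* The true time-averaged share is about 0.30. The note-weighted average is 0.30, 0.38 and 0.46 at b = 0, 0.5 and 1.0.
- *Contact intensity varying between people, unrelated to severity (b = 0.5).* As the log-SD of intensity goes from 0 to 0.5 to 1.0, the correlation of raw symptom-term counts with true mean severity falls from 0.82 to 0.50 to 0.26. Their correlation with intensity is 0.75 and 0.85 at log-SD 0.5 and 1.0. A per-note share has a correlation of about 0 with intensity, so it removes this between-person effect, but not the distortion in the previous item.
- *Truncation (b = 0.5).* Records that start at a crisis (severity above 1.5) show a fitted 24-month change in symptom share of −0.33, against 0.00 for records that start at an arbitrary month. That fall is recovery from the crisis at entry. It reflects where the record begins, not a different long-run course.

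**The case against.** The strongest reply is that the method is left open. The matrix is introduced as an example. Phase 1 exists to compare preprocessing and modelling strategies, and Phase 2 applies what Phase 1 develops. Aggregation windows and covariates commonly belong in a statistical analysis plan, which is not at hand. All of this is correct: a reader might infer that the protocol commits to pooling notes unweighted and unadjusted, and it does not say so. What it does fix is the source, unequal look-back and the antecedent reading, and no later choice of model restores text from before first contact.

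There are also real checks. Section 1.1 expects correlation with structured measures of the same constructs, section 3.10 uses visit data and scales for validation, and section 7.5 provides for human review of themes. Class prediction follows Objective 2, whose predictors include treatment factors and psychopathology. A reader might infer that the hypothesis could be supported with the trend measuring no functioning at all; given these checks, that goes too far. They are nevertheless partial. Scales held in the record are also collected at contacts, and contact could inflate a correlation with prospective scales. Linkage to provincial data (section 3.9) adds events outside CAMH for those who consent, but not notes.

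Two further points stand. That notes are denser in admissions is an inference, not protocol text. And contact is partly a consequence of clinical state, so adjusting for note count can remove real signal.

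**Conclusion.** The point holds for the exploratory objective only. As section 5.0 describes the analysis, note-based trends can correlate with outcome or predict class through contact intensity and length of record, and nothing stated would let a reader tell that apart from functioning.

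Truncation at first CAMH contact follows directly from the source. The over-weighting of unwell periods rests on the inference that contact rises with illness. Its size is unknown: the 28% to 72% note shares are illustrations at one outpatient note a month, fall to 8% or 16% under another assumed rate, and measure bias directly only if notes are pooled without weighting. The simulation shows the direction of the effects on assumed values, not their size in this cohort.

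A reader might infer that the three co-primary trajectory analyses or the power statements are compromised. They are not: those trajectories come from scheduled assessments of the RAS, WHO-DAS and PSP, and the power statements do not involve the notes. The change is worth making because it is cheap and decides how a positive exploratory result may be read.

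**What to change.** In sections 3.10 and 5.0:

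1. Summarise topic weights to one value per person per fixed window, for example six months to match the study visits. Treat windows without notes as unobserved, not as absence of symptoms.
2. Restrict the antecedent-marker analysis to participants with a stated minimum pre-enrolment CAMH record.
3. Report the correlations and the class prediction with and without visit frequency, inpatient or outpatient setting and length of CAMH record. Claim an antecedent marker of functioning only if the text trend adds to these.
4. Do not make adjustment for note count the only analysis, because contact partly reflects clinical state.

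The cost is mainly wording and some extra analysis, since encounter data are already to be extracted and linked. The downside is that new patients with little or no prior record leave the antecedent analysis, which narrows its coverage of illness stages. They have little antecedent text to contribute, and the number excluded should be reported.

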**3.11 Needs assessment of interventions to improve outcomes and reduce disability in SSDs**

Within the cohort there is a unique opportunity to conduct a needs assessment of the currently available and accessible evidence-based interventions and promising practices that may improve outcomes and reduce disability in clinical populations with SSDs. We aim to obtain input from study participants on early trajectory data and predictors to identify specific gaps in care and needs that may not yet be met by evidence-based services offered at CAMH, or by CAMH partners, or can be improved upon.

Data collected during the 1st year of the study period will be analyzed with the goal of identifying preliminary trajectories. The distribution of predictor variables measured during this period will also be described (e.g., measures of physical health, cognitive functioning, medical comorbidities). Although it is possible that data from these early time points may not map exactly onto the final trajectories identified at the end of the cohort, it is anticipated these early data points will provide information on specific areas of need and or service gaps within the cohort. For example, differential service use patterns associated with comorbidities, baseline cognitive functioning, as well as metabolic and physical health profiles may be elucidated from these early data and may be important predictors of both preliminary categorization of function and recovery and final trajectories.

Following identification of preliminary trajectories and key predictors, participants will be invited to participate in a needs assessment in the 2nd year of the study. The focus of this needs assessment will be to identify specific gaps in functioning, care and services that are directly related to the initial trajectories. Information on service user experience with current services and treatment in conjunction with the presentation of initial trajectories will be used to determine whether gaps exist due to missing and/or misaligned services, process issues, or contextual issues. This process will occur in both individual and group settings using a semi-structured format. An inductive thematic analysis will be undertaken to identify and report emergent themes and patterns.

The outcomes of this process will also identify potential targets for future co-design treatment interventions that will be the focus of an adjunct to this study (and to be submitted at the time for REB review).

**4.0 DATA MANAGEMENT PROTOCOLS**

Demographic, clinical assessment, cognitive, health, socio-environmental, and outcome data via CAMH’s Research Electronic Data Capture (REDCap) platform. All MRI data will be uploaded to XNAT and automated pipelines used for standardized processing and QA/QC procedures. Labkey will be used to support tracking and management of biological samples and genetic analysis data. All data will be linked via each participant’s unique study ID. Data access controls will be utilized to restrict access to each tool to study team members requiring access to this data. Central data management will utilize the CAMH Neuroinformatics Platform. With informed consent from study participants, data from participants with an Ontario health card number will be linked with health care utilization data through the Institute of Clinical Evaluative Sciences (ICES).

Data collection will take place either in-person, remotely via REDCap survey link for self-report measures where applicable, or virtually through the use of the Cisco Webex videoconferencing platform, depending on participant preference, availability, and suitability for in-person study visits based on pandemic-related hospital guidelines for clinical research. Data will be collected on electronic or paper-based forms, which are identified by a unique participant ID number, protocol ID number, and protocol phase and visit, and are entered into a secured REDCap database housed at CAMH which will be managed by the study team. REDCap is a secure, web-based platform, which is used world-wide to collect all types of data ranging from research, to clinical, to operations and has features to support best practices for data confidentiality, security, data validation, auditing, and data backup.

A protocol data collection schedule will be used to monitor participant progress, missing assessments, and other protocol deviations during the study. Data entry screens will incorporate range checks or lists of valid responses for each item to ensure accurate data entry. Forms with missing or invalid data in key identifying fields will be referred back to raters for correction before entry. Other missing or invalid data will not prevent the form from being entered, but will be flagged for correction. Queries will be built around data entry and reports to review adverse events. Participant confidentiality will be maintained by restricting study data access to specified study personnel. Once data has been entered, an electronic audit trail will record all database changes. The database will reside on a central server, and all server data is backed up on a regular basis. Outside access to the server is restricted by a firewall. At the conclusion of the study, all study data will be archived and retained for the full period required by regulations and according to CAMH SOPs.

Health administrative data linkage will be done through ICES, a prescribed entity under Ontario’s Personal Health Information Protection Act that follows the policies and procedures for privacy protection and data security approved by Ontario’s Information and Privacy Commissioner. Participants’ primary data collected through this study will be securely transferred to ICES from the CAMH server via secure data transfer to be linked with administrative data. This secure, encrypted channel is established by ICES and managed by authorized ICES individuals. After assignment of a unique ICES identifier all identifiers will be removed and only de-identified data will be used to conduct analyses. Only ICES-approved and trained analysts are entitled to conduct primary data analysis in secure zones within ICES facilities. Data will only be accessed internally, using a password-protected monitored user account. Only aggregate results may be removed from this secure server. ICES practice is to destroy any data transferred for linkage at 180 days and to retain the coded data used for research for 10 years. The lookback period within the ICES health administrative data examined for individuals who have provided consent will either be their date of birth or when they first became eligible for OHIP coverage (e.g., if they moved to Ontario from another province or country). As a prescribed entity under PHIPA, ICES is permitted to hold and analyze data that are identifiable, but to only report publicly in a non-identifiable format.

*Data sharing permission from participants to reduce participant burden*

We will acquire permission from study participants to use data already captured in their electronic medical record. Many of the clinical services at CAMH where participants will recruited for this study already utilize some of the rating scales and collect some amount of sociodemographic, educational, and cognitive information as part of routine clinical care. For study participants where this information has already been collected as part of their routine clinical care, we will endeavour to utilize this already collected information rather than repeating these assessments. This will reduce participant burden by shortening the research assessment duration for study visits. In addition, we will acquire permission from study participants to share data collected as part of this study with other research studies they may take part in at CAMH, as well as permission for results of those studies (e.g., imaging, genetics, and laboratory assessments) to be shared with this study. This will serve to also reduce participant burden by shortening research assessment durations, as well as leverage other concurrent research studies to augment the biomarker collection plan for this study. Finally, we will also acquire permission from study participants to share the results of their research assessments from this study with their clinical team. Many of the clinical services at CAMH where participants will recruited for this study already utilize some of the rating scales (i.e., BPRS, CGI, PSP, SAS, BARS, AIMS, as well as self-report assessments including the WHO-DAS, AUDIT-C, NIDA Modified ASSIST, CAMH Tobacco Screener) and collect some amount of sociodemographic, educational, and cognitive information (i.e., CAMH Health Equity Form, BCATS), as well as physical health assessments (i.e., height, weight, BMI, waist circumference, metabolic laboratory assessments) as part of routine measurement-based clinical care. Other measures from this study not routinely collected may also be useful to their clinical team in supporting the participant’s clinical care.

*Open Science*

The PREDICTS Study will implement open science by utilizing processes and data governance being established by the BrainHealth Databank to enable and promote data sharing and reuse with researchers at CAMH and around the world. This includes implementation of study data management processes to ensure that study data adhere to the FAIR data principles – Findable, Accessible, Interoperable, and Reusable, collection of common data elements to facilitate data standardization and harmonization as appropriate, and inclusion of standardized informed consent to enable future data sharing and secondary use of data.

To support data sharing, a PREDICTS cohort explorer dashboard will be created to allow users to explore available data and formulate data access requests. Initially this dashboard will be used by PREDICTS researchers across core projects and data modalities to answer primary study questions. In the future, the PREDICTS study cohort explorer dashboard will be made available to other researchers at CAMH and around the world to enable secondary research studies. All information entered into these databases will be free of identifying information. Data access to researchers conducting secondary studies will be granted once appropriate approval, as defined in the BrainHealth Databank Data Access Policy, has been obtained.

*Confidentiality*

There is a potential risk of breach of confidentiality that is inherent in all research protocols. Breach of confidentiality will be minimized by the staff who will maintain research data (identified only by participant code number not related to name, or date of birth) in separate charts and a dedicated password protected electronic database. A list of participant names, their ID numbers, and information about how they can be reached will be kept in a separate locked cabinet with access only to study personnel authorized by the PIs. Procedures have been established, and will be followed, to minimize the risk of breach of confidentiality. Procedures to maintain confidentiality include: (1) formal training sessions for all research staff emphasizing the importance of confidentiality; (2) specific procedures developed to protect participants’ confidentiality, and (3) formal mechanisms limiting access to information that can link data to individual participants. All information obtained from participants will be kept as confidential as possible. Computer based files/data will be entered into password-secured databases and paper-based files will be stored in a secure location. These data will only be accessible to personnel involved in the study and they will abide by confidentiality regulations of the REB. The ethics committee will be granted direct access to the study participants’ original medical records for verification of clinical trial procedures and/or data, without violating the confidentiality of the participants, to the extent permitted by the law and regulations.

